# Does sensorimotor upper limb therapy post stroke alter behavior and brain connectivity differently compared to motor therapy? Protocol of a phase II randomized controlled trial

**DOI:** 10.1186/s13063-018-2609-4

**Published:** 2018-04-20

**Keywords:** Stroke, Upper limb, Sensorimotor function, Randomized controlled trial, Functional connectivity

## Abstract

**Background:**

The role of somatosensory feedback in motor performance has been warranted in the literature. Although sensorimotor deficits are common after stroke, current rehabilitation approaches primarily focus on restoring upper limb motor ability. Evidence for integrative sensorimotor rehabilitation approaches is scarce, as is knowledge about neural correlates of somatosensory impairments after stroke and the effect of rehabilitation on brain connectivity level. Therefore, we aim to investigate changes in sensorimotor function and brain connectivity following a sensorimotor therapy program compared to an attention-matched motor therapy program for the upper limb after stroke.

**Methods:**

An assessor-blinded randomized controlled trial will be conducted. Sixty inpatient rehabilitation patients up to eight weeks after stroke will be included. Patients will be randomized to either an experimental group receiving sensorimotor therapy or a control group receiving attention-matched motor therapy for the upper limb, with both groups receiving conventional therapy. Thus, all patients will receive extra therapy, a total of 16 1-h sessions over four weeks. Patients will be assessed at baseline, after four weeks of training, and after four weeks of follow-up. Primary outcome measure is the Action Research Arm Test. Secondary outcome measures will consist of somatosensory, motor and cognitive assessments, and a standardized resting-state functional magnetic resonance imaging protocol.

**Discussion:**

The integration of sensory and motor rehabilitation into one therapy model might provide the added value of this therapy to improve sensorimotor performance post stroke. Insight in the behavioral and brain connectivity changes post therapy will lead to a better understanding of working mechanisms of therapy and will provide new knowledge for patient-tailored therapy approaches.

**Trial registration:**

ClinicalTrials.gov, NCT03236376. Registered on 8 August 2017.

**Electronic supplementary material:**

The online version of this article (10.1186/s13063-018-2609-4) contains supplementary material, which is available to authorized users.

## Background

Patients surviving a stroke encounter a variety of impairments, one of which is a unilateral sensorimotor impairment in the upper limb. Somatosensory impairments are defined as deficiencies in the sensation arising from skin, muscles, or joints [1]. These impairments can consist of a deficit in discriminative abilities, proprioception, or detection of sensation such as light touch, pressure, or pain. Sensorimotor deficits at one week post stroke lead to limitations in activities of daily living and restrictions in participation in society [2]. In general, approximately half of the patients admitted to a stroke rehabilitation unit encounter somatosensory impairments [3, 4]. A recent study showed that at one week post stroke, 78% have a single or combined sensorimotor impairment in the affected upper limb [5].

Evidence-based guidelines for therapy aimed at restoring motor impairments do exist but, as yet, therapy-mediating somatosensory impairments are still scarce. A 2010 Cochrane review by Doyle et al. [6] on “interventions of sensory impairments in the upper limb after stroke” concluded that “*there is insufficient evidence to reach conclusions about the effects of interventions included in this review.”* In 2011, results from a randomized controlled trial (RCT) by Carey et al. [7] investigating the effect of upper limb sensory discrimination training on somatosensory function after stroke showed a significant effect of sensory discrimination training compared to general sensory exposure in chronic stroke [7]. Although the evidence for the effect of somatosensory therapy on somatosensory function is increasing, to our knowledge, only two case-series studies have investigated its effect on motor function [8, 9]. A preliminary study reported results of two patients who received sensorimotor stimulation training consisting of passive mobilization, sensory stimulation by means of an electric toothbrush for vibration, and position training for proprioception. The box and blocks test and the 10-s test were conducted after each session and showed improvements [9]. Another preliminary study reported a case series of two patients receiving a sensorimotor program consisting of manipulation tasks with a sensory discrimination aspect, such as sorting plastic eggs of different weights [8]. Also, the latter study reported improvement in motor function after training. Further, neural sensory reorganization was found on functional magnetic resonance imaging (fMRI) and brain volume measurements for both participants after the sensorimotor discrimination program [8].

The key role of somatosensory feedback in motor control and function has been investigated. Somatosensory impairments are associated with poorer dexterity, manipulation abilities, and bimanual hand coordination skills [6, 10, 11]. Impaired surface friction discrimination is associated with longer grip-lift latency times and increased grip force regulation during a grip-lift and hold task [12]. Intervention studies investigating the effect of somatosensory stimulation on motor learning in healthy controls confirmed the sensorimotor coupling. One study investigated the effect of repetitive transcranial magnetic stimulation over the primary somatosensory cortex, inhibiting somatosensory function, on motor learning [13]. They reported less accurate tracking and a smaller learning effect for a motor task during stimulation. These effects persisted at the retention test, indicating the influence of somatosensory disruption on motor control and learning [13–15]. Translating these paradigms to post-stroke therapy and designing an integrative treatment consisting of combined and emphasized somatosensory and motor input could provide additional sensorimotor benefit over exercises focusing on pure motor activation.

Besides behavioral outcomes, brain connectivity analysis post treatment would provide insights in neural correlates of upper limb therapy. Neural reorganization associated with stroke has also been mainly investigated for motor impairments. Increased intrahemispheric and decreased interhemispheric functional connectivity is associated with motor deficits [16–19]. Recovery of motor function is reported along normalization of inter- and intrahemispheric functional connectivity within the sensorimotor network of humans and rats [20–22]. However, knowledge about altered functional connectivity associated with somatosensory impairments is still limited. Results from our group showed decreased inter- and ipsilesional intrahemispheric functional connectivity in patients in the acute phase with severely impaired somatosensory function compared to patients with mild to moderate somatosensory impairments (unpublished data). Additionally, recovery of sensory discrimination is shown to be associated with an increase in interhemispheric functional connectivity between primary somatosensory cortices and both thalami [23]. To date, brain connectivity alterations in the sensorimotor network after sensorimotor vs motor therapy have not been investigated.

The role of resting state functional connectivity to serve as predictor for stroke recovery is still unclear. A recent position paper on “biomarkers of stroke recovery” [24] from the stroke recovery and rehabilitation roundtable suggests developmental priority to research concerning the utility of resting state functional connectivity to predict treatment response. Both for motor and somatosensory function, some but insufficient evidence is available to support the inclusion of resting state functional connectivity as a biomarker in clinical trials at present [24]. More specifically, the predictive value of interhemispheric resting state functional connectivity at baseline can be investigated to determine its potential to serve as biomarker. The future inclusion of biomarkers as eligibility criterion in clinical trials will result in more homogeneity within the study population and a better estimation of treatment effect. Therefore, including brain imaging outcome parameters in clinical trials will provide insights in underlying mechanisms of therapy-induced effects at brain level as well as suggesting biomarkers to be considered for future clinical trials.

To summarize, somatosensory function plays an important role in motor learning and performance. Sensory discrimination therapy has a positive effect on recovery of somatosensory function post stroke but the effect on motor behavior and underlying brain connectivity alteration is not fully understood. Therefore, we will conduct a phase II RCT with two parallel groups to investigate the effect of sensorimotor vs motor therapy on sensorimotor function and brain connectivity. We hypothesize that after sensorimotor therapy, patients will show a greater improvement in sensorimotor function compared to patients receiving motor therapy. We further hypothesize that brain connectivity changes related to sensorimotor recovery will show increased normalization within the sensorimotor network compared to patients receiving motor therapy.

## Methods

### Study design

This study is an assessor-blinded multicenter RCT. Integrative and emphasized sensorimotor upper limb therapy will be compared to attention-matched motor upper limb therapy. Both groups will receive the same amount of therapy contact and training time as part of this therapy, in addition to conventional patient-focused inpatient rehabilitation. An overview of the study flow diagram is provided in Fig. 1. Unblinding of the assessor will not be permissible at any time point.

**Fig. 1 Fig1:**
[figure not shown]
Study *flow diagram*

The study is reported conform the SPIRIT (Standard Protocol Items: Recommendations for Interventional Trails) statement [24] (Additional file 1).

### Study setting

This multicenter RCT will be conducted by the University of Leuven (KU Leuven) at the stroke ward of two rehabilitation centers in Flanders, Belgium: University Hospitals Leuven (Campus Pellenberg) and Jessa Hospital (Campus Sint-Ursula, Herk-de-Stad).

### Participants

Sixty patients after first-ever unilateral, supra-tentorial stroke as defined by the World Health Organization [25] will be included after admission to the rehabilitation center with following inclusion criteria: (1) stroke onset within eight weeks; (2) presence of motor and somatosensory impairment in the upper limbs; (3) aged 18 years and older; and (4) providing substantial cooperation. Motor impairment is defined as a score < 52/57 on the Action Research Arm Test (ARAT). Somatosensory impairment is defined as a negative score on the standardized somatosensory deficit composite score [7].

Patients with following criteria will be excluded: (1) musculoskeletal or other neurological disorders with stroke-like symptoms; (2) severe communication or cognitive deficits; (3) the presence of contra indications for undergoing an MRI brain imaging protocol; and (4) no informed consent.

### Procedure

An overview of the study flow diagram is provided in Figs. 1 and 2.

**Fig. 2 Fig2:**
[figure not shown]
Schedule of enrolment, interventions, and assessment following SPIRIT guidelines. T1 baseline assessment, T2 assessment after four weeks of intervention, T3 assessment after four-week follow-up (eight weeks after start of intervention)

##### Sensorimotor therapy

The sensorimotor therapy will consist of 30 min of somatosensory discrimination training and 30 min of integrative and emphasized sensorimotor training per session in a one-to-one setting. The sensory discrimination training will be based on the SENSe approach [7] and will include three sensory discrimination tasks: texture discrimination; limb position sense; and tactile object recognition. Texture discrimination will be trained using progressively and variated surface characteristics such as fabric, wallpaper, plastic, and sandpaper. Limb position sense will be trained across a wide range of upper limb positions and include for instance full flexion, full extension, and neutral position of the index finger, wrist, and elbow. Tactile object recognition will be trained using different objects varying of shape, size, weight, texture, hardness, and temperature such as bottles with differences in amount of contained fluid, cutlery, plates of different materials such as wood, plastic, metal, coins of different sizes, etc. An overview of examples of possible exercises can be found in Additional file 2. The 30-min sensorimotor training per session will be the same individually tailored motor therapy as described below, but with full integration of sensory discrimination training aspects such as reaching towards and bringing to the mouth the same bottles with varying weights used in the sensory part of the therapy with the additional task to determine the weight of the bottle. A well-defined package of exercises has been developed in order to standardize this therapy approach.

##### Motor therapy

The motor therapy will consist of 30 min of cognitive and attention-based table top games and 30 min of motor training per session in a one-to-one setting. The cognitive attention-based therapy will consist of table top games such as chess, rush hour, or other smart games, all performed with the unaffected upper limb. Individually tailored motor therapy consists of a unilateral motor exercise program for the affected upper limb, while seated at a table, under supervision of a therapist to match the therapy and intensity provided in the sensorimotor therapy group. This 30-min motor arm training will be based on a set of standardized exercises which comprise of task-related practice for gross movements and dexterity including different grips and selective finger movements, and training in daily life activities, however without any attention to sensory discrimination training [28]. A complete package of exercises has been developed for a recently conducted trial [28] and this will also be applied in this trial.

#### Safety

We collect adverse events from our participants through asking our patients before the next treatment or assessment session whether any event occurred since the previous session. Events formulated will be evaluated for causality and if linked to the treatment provided, this will be reported as an adverse reaction or serious adverse reaction (in case of a life-threatening complication, prolonged hospitalization, or persistent and significant remaining disability) although the latter is unlikely based on the type of treatment provided in this trial.

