Our primary outcome measure is the ARAT. The ARAT consists of four subscales: grasp; grip; pinch; and gross movement to evaluate the activity level of the upper limb. A total score between 0 (loss of motor performance) and 57 (good motor performance) can be obtained. Adequate reliability and validity are reported in the literature [32]. We hypothesize that combined and emphasized sensorimotor therapy will benefit motor function more than pure motor therapy due to sensorimotor coupling. Therefore, we have chosen the ARAT as measurement of upper limb function, which is widely used in research as primary outcome measure and a recommended measurement tool for upper limb activity [33].

Secondary motor outcome measures are the Fugl-Meyer assessment - upper extremity part (FMA-UE) [34] at function level according to the ICF model [35], the Nine-Hole Peg Test (9HPT) [36] evaluating dexterity, the Stroke Upper Limb Capacity Scale (SULCS) [37] investigating basic and extended upper limb activity, and the Abilhand questionnaire (ABIL) for perceived manual ability [38].

Secondary somatosensory outcome measures include the Erasmus-modified Nottingham Sensory Assessment (Em-NSA) [39] and perceptual threshold of touch (PTT) [31]. Additionally, the composite standardized somatosensory deficit score [40] consisting of the tactile discrimination test (TDT) [41], wrist position sense test (WPST) [42], and functional tactile object recognition test (fTORT) [43] will be performed to investigate somatosensory function.

All tests have good psychometric properties. Additional file 3 provides more information about content and psychometric properties of the outcome measures. Finally, brain imaging is conducted and will consist of a standardized protocol including an anatomical scan and a resting-state fMRI scan. A total of 30 parallel slices of 4-mm thickness and transverse orientated with no interslice gap will be obtained for the resting state fMRI scan. Scanning parameters include echo time (TE) = 33 ms, repetition time (TR) = 1700 ms, flip angle = 90°, field of view (FOV) = 230 mm, matrix = 64 × 64, and duration = 7 min. Patients will be in the supine position with eyes open and fixating on a cross and will be asked to not think about anything in particular or fall asleep.

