Despite the strengths of our study, some challenges remain. Good clinical assessments for motor and somatosensory function often lack sensitivity to change. We composed an extensive and established assessment battery of tests covering both function and activity level. Both assessments of upper limb motor (FMA) and somatosensory (Em-NSA) function as well as more specific assessments for dexterity (9HPT), proprioceptive (WPST), or touch discriminative function (TDT) will be included in the protocol to cover a wide spectrum of somatosensory and motor function, and activity level performance of patients [34, 36, 39, 41, 42]. Additionally, the inclusion of the perceptual threshold of touch as an outcome measure for light touch will address the sensitivity since it is a more objective and a ratio-scaled outcome measure [31]. For patients with severe communication difficulties, assessment of somatosensory function may be challenging. In addition, attention deficits could influence somatosensory assessment. When somatosensory function is decreased and patients do not pay attention to the somatosensory stimuli during assessment, they could incorrectly report not to feel the stimulus. Therefore, patients with severe communication and attention disabilities are excluded from our trial, which will limit the generalizability of our findings.

In summary, this trial will investigate the behavioral and neural correlates associated with stroke-induced sensorimotor therapy for the upper limb. More specifically, the effects of therapy on clinical outcome and functional connectivity in rest is the scope of this study. Thus, our findings will provide novel insights in the neural base of recovery of upper limb sensorimotor function after stroke.

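### The Safety section names patient questioning as its only source of adverse events, in patients who all have a sensory deficit of the upper limb; therapist observation should be added identically in both arms

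*Protocol article*

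**What the plan says.** All references are to the protocol article.

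- **Safety.** The collection method is stated outright: "We collect adverse events from our participants through asking our patients", ahead of each further treatment or assessment, about anything that has happened since the last contact. The next step is also fixed: "Events formulated will be evaluated for causality and if linked to the treatment provided", the event is reported as an adverse reaction or a serious one. No other source is named.
- **Participants.** Entry requires "presence of motor and somatosensory impairment in the upper limbs". The sensory part has its own definition: "Somatosensory impairment is defined as a negative score on the standardized somatosensory deficit composite score". Under Outcome measures that composite is described as "consisting of the tactile discrimination test (TDT) [41], wrist position sense test (WPST) [42], and functional tactile object recognition test (fTORT".
- **Randomization and Data analysis.** Neglect is a stratification factor and a planned subgroup, so patients with neglect are enrolled. No prevalence is given.
- **Sensorimotor therapy.** Half of each session is sensory discrimination training. Its textures include sandpaper, and object recognition uses "different objects varying of shape, size, weight, texture, hardness, and temperature". The other half is the motor programme with sensory tasks built in.
- **Motor therapy.** Half of each session is table-top games played with the unaffected limb. The other half is motor training of the affected limb.
- **Intervention.** A therapist works one-to-one with each patient for 16 sessions and keeps a paper record of the content of every session.

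**The concern.** Asking the patient works best for events the patient notices. Here every patient has impaired discrimination, position sense or object recognition in the upper limb, and some also have neglect, which makes seeing a minor injury a less dependable backup to feeling it. A small abrasion or overuse problem in that limb is the kind of event that questioning alone may not bring out.

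The therapist sits with the patient at every session and already fills in a record, but the Safety section does not make that observation a source of adverse events. If few or no reactions are reported, a reader could not tell how far this reflects safety and how far it reflects the way events were sought. The primary outcome and its analysis are not affected. What is at stake is how much the trial's safety statement can carry.

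**Working it through.** The article gives no event rate, detection rate or safety target, so there is no figure to reproduce. The check has three parts.

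**1. Exposure of the affected limb (from the article, with one assumption).** Each arm has 30 patients and 16 one-hour sessions. The article does not say outright which hand does the sensory discrimination training; I assume the affected one.

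- Sensorimotor arm: 30 + 30 = 60 minutes per session. 16 × 1 h = 16 h per patient; 30 × 16 h = 480 h in the arm.
- Motor arm: 30 minutes per session, since the games use the other limb. 16 × 0.5 h = 8 h per patient; 30 × 8 h = 240 h in the arm.
- Ratio: 480 / 240 = 2.

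**2. What incomplete detection does within one arm (rates assumed).** Let *p* be the true per-patient risk and *s* the share of events detected. The chance that no event is recorded among 30 patients is (1 − *ps*)^30. With *p* = 10%:

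| *s* | *ps* | chance of none recorded |
|---|---|---|
| 1 | 0.100 | 0.90^30 = 4% |
| 0.5 | 0.050 | 0.95^30 = 21% |
| 0.25 | 0.025 | 0.975^30 = 47% |

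Seen the other way, if 0 of 30 patients have a recorded event, the one-sided 95% upper bound on the recorded risk is 1 − 0.05^(1/30) = 9.5%. Dividing by *s* gives the bound on the true risk:

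| *s* | upper bound on true risk |
|---|---|
| 1 | 9.5% |
| 0.8 | 11.9% |
| 0.5 | 19.0% |
| 0.3 | 31.7% |

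**3. What it does to the comparison of arms (rates assumed).** Take true risks of 20% (sensorimotor) and 10% (motor), in line with the exposure ratio of 2 if risk is proportional to hours of training.

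- Equal detection, *s* = 0.5 in both arms. Recorded: 30 × 0.20 × 0.5 = 3.0 against 30 × 0.10 × 0.5 = 1.5. Missed: also 3.0 against 1.5. The recorded risk ratio is 3.0 / 1.5 = 2.0, the same as the true one. Twice as many events are lost in the sensorimotor arm, but the same proportion.
- Unequal detection, *s* = 0.5 against 0.8. The recorded risk ratio is 2.0 × 0.5 / 0.8 = 1.25. The ratio is pulled towards 1 only in a case like this.

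The article describes the same eligibility, question and timing for both arms. Nothing in it supports the unequal case over the equal one.

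**The case against.** The strongest reply is that this is a short safety paragraph in a journal article. It does not exclude other sources, and the full protocol may name them. This has some force, and for that reason the point is confined to the only route named. But the paragraph is not silent: it states a method and says what then goes forward for causality review. A stated rule can be judged as stated.

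Several stronger readings are tempting and are not supported:

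- **That patients are selected for being unable to feel the limb.** Entry rests on a composite of discrimination, position sense and object recognition. Loss of pain or temperature sense is not required.
- **That the article concedes patients misreport events.** The Discussion does say of patients that "they could incorrectly report not to feel the stimulus", but this concerns sensory testing and requires inattention as well as reduced sensation. The article then cites the exclusion of patients with severe communication or attention problems, which lessens the difficulty in part. It does not remove patients with neglect.
- **That harm is under-counted mainly in the experimental arm.** Longer exposure bears on how many events occur, not on the share detected. With equal detection the risk ratio is kept.
- **That the materials are a known hazard.** Sandpaper and temperature-varied objects are listed, but no temperature range is given and the examples are everyday items. Thermal injury is a possibility only.
- **That an unsafe therapy would pass into phase III.** The sample size section promises only a sample size calculation for that trial and states no safety gate.

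A further objection is that the therapist knows the allocation, so therapist observation could itself differ by arm. That is a real cost. It does not defeat the change, because the same unblinded therapist gives the sessions in both arms and is probably the person who asks the question before each treatment now.

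**Conclusion.** The point holds in a limited form. The single named route fits this population poorly, and minor skin or overuse events in the affected limb may be missed in both arms. More may be missed in number in the sensorimotor arm, about twice as many if the sensory training uses the affected limb, risk is proportional to hours of training, and detection is equal. None of these three conditions is established by the article.

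The size of the problem is unknown. The 4%, 21% and 47% figures and the bounds from 9.5% to 31.7% show how sensitive a clean safety record in 30 patients is to detection; they do not estimate what this trial will miss. A reader might infer that harm is shown to be under-reported, or that detection is worse in the experimental arm. The document supports neither. This is a cheap improvement to safety reporting and leaves the efficacy analysis untouched.

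**What to change.** Amend the Safety section so that, in the same way in both arms, adverse events come from:

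1. the patient's answer, as now;
2. the therapist's observation of the treated hand and arm, entered on a fixed checklist line in the paper record already kept for every session;
3. a check of the ward record at T2, where available.

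Send events from all three sources to the causality review, and report them by arm and by source. Reporting by source lets readers see what questioning alone would have found.

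Cost: one line per session, which is 60 × 16 = 960 entries if all sessions take place, and a short record check per patient; no extra staff. There are two downsides. More minor events will be recorded. The observing therapist is not blinded, so the checklist wording and the moment of observation should be standardised and identical in both arms, and the limitation stated when results are reported.
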